## Abstract

**Introduction:**

Epidemiological studies show that increased physical activity is linked to a lower risk of breast cancer and mortality. As a result, physical activity can significantly improve patients' quality of life (QOL) both during and after therapy.

Many breast cancer patients demonstrate a decrease in cognitive capacity, referred to as the symptom-complex cancer related cognitive impairment (CRCI). Most frequently reported impairments are mild to moderate deficits in processing speed, attention, memory, and executive functions. Cognitive symptoms persist for months or even years, following medical treatment in roughly 35% of afflicted people, impairing everyday functioning, limiting the ability to return to work, and lowering the overall QOL. Recent studies point toward a key role of inflammatory pathways in the CRCI genesis. Attention to physical activity as a potential supportive care option is therefore increasing. However, evidence for the positive effects of exercise on preventing CRCI is still lacking.

**Patients and Methods:**

Against this background, the prospective, two-arm, 1:1 randomized, controlled trial investigates the influence of first line chemotherapy accompanied by exercise training on preventing CRCI in 126 patients with breast cancer at the local University Hospital. The study will evaluate biomarkers and secondary assessments suspected to be involved in the pathogenesis of CRCI in addition to objective (primary outcome) and subjective cognitive function. CRCI is believed to be connected to either functional and/or morphological hippocampal damage due to chemotherapy. Thus, cerebral magnetic resonance imaging (MRI) and hippocampal volume measurements are performed. Furthermore, a specific neuropsychological test battery for breast cancer patients has been developed to detect early signs of cognitive impairments in patients and to be integrated into practice.

**Discussion:**

This study will explore how a long-term supervised exercise intervention program might prevent CRCI, enables optimization of supportive care and objectifies limits of psychological and physical resilience in breast cancer patients during and after chemotherapy treatment.

**Trial Registration:**

ClinicalTrials.gov: Identifier: NCT04789187. Registered on 09 March 2021.

## Introduction

Despite the efficacy of breast cancer treatments, chemotherapy has severe side effects on patients' cardiovascular and metabolic systems and quality of life (QOL). Some adverse effects can be acute, occurring primarily during treatment, whereas others may have a delayed onset and persist for years after the end of treatment (1).

The variability of these side effects is widespread. Chemotherapy often leads to nausea, vomiting, depression, reduced bone-mineral density, cardiac toxicity, and cancer-related fatigue (2, 3).

Targeted exercise programs reduce several diseases and treatment-related side effects, including fatigue, depression, and lymphedema, mentioned above, besides increasing completion rate (4, 5). Therefore, exercise regimens can improve patients‘ QOL during and after therapy (6).

Cancer-related cognitive impairment (CRCI) – formerly termed as “Chemobrain” – can be observed before, during, and after treatment in breast cancer patients (7–9).

Mild to moderate deficiencies in learning, memorization, processing speed, and executive processes (10) are the most commonly reported impairments, and they significantly affect patients' QOL (11, 12). The percentage of breast cancer patients reporting cognitive impairments varies between 17 and 75% (13–15). This difference may be driven by varying assessment time points, assessment methods, criteria of cognitive impairment cut-offs, and various treatment/intervention regimens as well as interactions with correlating side effects, such as depression, and fatigue (13).

Although information about the underlying mechanisms of CRCI is still sparse. Investigations conducted in the past decade suggest a multifactorial genesis (16, 17).

Preclinical studies have shown that cytostatic drugs and radiation directly impair and damage different cell populations (e. g., neuronal progenitor cells and oligodendrocytes) (18) in the central nervous system (CNS). Clinical investigations, including microscopic and molecular findings, have revealed substantial reductions in gray and white matter volume and integrity (13, 19–26). These effects are not confined to treatments and drugs that can penetrate the blood-brain-barrier directly, suggesting mechanisms that are more complex.

According to recent literature, most likely indirect effects are disease- or therapy-related. They may translate to systemic inflammatory stimuli that penetrate the blood-brain-barrier causing functional and structural damage, and hence cognitive impairments (27). The role of systemic inflammation in this context has been accepted as a key player in the pathogenesis of neuropsychiatric diseases, and it demonstrates the delicate interplay between immune, nervous and central nervous systems in various pathological conditions (28).

Accomplishments in neuroscientific research conducted in humans and rodents have indicated that physical activity and exercise constitute a conservative and effective treatment method especially in psychiatric disorders such as major depression. Therefore, these activities have become a focus of interest for supportive therapies in oncology patients to prevent cognitive impairment (29–32).

Increased physical activity following diagnosis has been linked to primary cancer prevention and decreased mortality in oncology patients. Physical exercise interventions, therefore, became an integral and important part of supportive therapy in cancer patients (33), since they effectively reduce several side effects such as fatigue (34) and depressions as well as lymphedema and improve patient's fitness and QOL (35, 36).

Through a survey of the published literature, our group has found that exercise therapies considerably improve and preserve cognitive performance in healthy adults (27, 31, 37–39) and patients in clinical settings (40). Exercise appears to significantly reduce CRCI, according to preliminary findings. Preclinical studies have shown that physical activity reduces (neuro-) inflammatory stress in the long run and raises circulating and central levels of neuronal growth factors (41–47).

In this context, the most frequently investigated brain structure is the evolutionarily highly conserved hippocampus, which is involved in multiple cognitive activities such as learning, memory, and pattern recognition. It became a focus of interest in recent studies investigating CRCI, due to its sensitivity, ability to perform neurogenesis, and integration in various psychiatric and neurodegenerative disorders (37, 38, 48, 49).

Therefore, the majority of the findings mentioned above concern to the hippocampus, where the influence of physical exercise and neurogenesis has been associated with an increase in hippocampal volume and an enhanced memory function (31, 50, 51).

Regarding the type and intensity of the implemented exercise regimen, comprehensive reviews have shown that higher intensity exercise regimens may have superior effects on cognition, and they may be linked to physiological underpinnings compared to low or moderate aerobic exercise interventions (50, 52–59). In a randomized pilot trial Lee et al. (60), noticed that high-intensity interval training (HIIT) during chemotherapy was safe and feasible for women with breast cancer (60). Mijwel et al. (55) used HIIT in their training regimen demonstrated its efficacy in breast cancer patients undergoing chemotherapy (55). HIIT appears to be highly effective in minimizing side effects and is more efficient in improving functional cognitive impairments than an aerobic exercise intervention alone (36, 55–57).

As mentioned earlier, the symptom-complex related to CRCI is highly heterogeneous and varies substantially from patient to patient. Although, stated previously, the hippocampus is essentially involved in most of the CRCI related activities. We, therefore, use the California Verbal Learning Test (CVLT) to measure the primary endpoint of the conducted trial – neurocognition regarding learning, memorizing, processing speed, and executive functions because of its high sensitivity to hippocampal related impairments (61, 62). Brain magnetic resonance imaging (MRI) and hippocampal volumetry is used in conjunction with potential structural abnormalities (26, 63).

In addition, a specific neuropsychological test battery for breast cancer patients has been developed, which will help to specify and detect early signs of cognitive impairment in patients and will be integrated into a new standard of treatment.

Unfortunately, exercise trials in the context of CRCI have several methodological limitations. The majority of studies (59, 64–66) conducted to date were small in cohorts and time, were not randomized, used a variety of unstandardized objective and subjective cognitive assessments, provided no information on physiological/biological changes, and most essentially did not include imaging techniques to screen for structural correlates in terms of cognitive impairment. Incompliance and lack of adherence in the intervention group are common problems, also when seen to be correlating directly with the median age of study cohort, entity of cancer and especially the type and administration of the exercise intervention (supervised/unsupervised) (67, 68).

Therefore, the ECCO-study bridges the gap between conducted exercise trials by summarizing all findings to CRCI up to this time and integrating them into a randomized controlled trial.

The aim of this study is to investigate the effects of an additional 12 months individualized and supervised HIIT based training program, in contrast to only giving out general physical activity recommendations, on cognition in patients with diagnosed local breast cancer receiving neo-/adjuvant chemotherapy. Secondary aims are to determine the effects of the intervention on physical performance, common cancer related side effects (e.g., fatigue, emotional and physical well-being and QOL), structural changes of the brain, as well as potential underlying biomarkers.

Therefore, we hypothesize, that constant physical activity and additional supervised HIIT in the intervention group results in less cognitive impairment compared to the control group. Hence, the mean (sub)scores “total trial,” “short delay” and “long delay” of the CVLT after 12 months of intervention are hypothesized to be higher in the intervention- than in the control group.

## Methods

The Exercise, Cancer and Cognition (ECCO) study was designed as a randomized controlled trial to investigate the impact of a long-term physical activity program on CRCI in patients receiving adjuvant/neoadjuvant breast cancer treatment.

The ECCO study is a monocentric two-arm 1:1 randomized controlled trial (RCT), including a 12-month intervention and control group. A detailed study-flow is shown in Figure 1. The exercise interventions start within the first week of chemotherapy and last for 12 months. The study protocol was approved by the local ethics committee of Upper Austria (Austria) (1191/2018) and registered with the WHO trial register (reference number: NCT04789187). Any modifications to the protocol, which had an impact on the realization of the study, on benefits and harms of the participants, on study objectives and design, on sample size or study procedure, required a formal amendment to the Ethics Commission and had been approved. Participants are assigned to one of two groups: an exercise intervention arm (A) and control arm (B). Group A is motivated to fulfill the general physical activity recommendations (individual heart rate definition and strength training advice, home based) (69) and should perform a supervised high intensity interval training (HIIT, center based) once a week in addition to regular care. The control arm (B) receives regular care and general physical activity recommendations. Both groups will follow the same recommended physical activity guidelines, but in contrast to the intervention arm, the control group does not receive any individual heart rate suggestions and strength training material.

**Figure 1 F1:**
[figure not shown]
Study flow.

### Study Population and Recruitment

Patients are recruited at the department of hematology and internal oncology of the Kepler University Hospital in Linz (AUT). Patients diagnosed with local breast cancer receiving neo-/adjuvant chemotherapy and not fulfilling any exclusion criteria listed in Table 1 are advised by the attending physicians and recruited for study participation. Patients receive a detailed description of the study, can ask any question, and are included in the planned research program only after written consent, according to the ethics committee's approval. Patients can withdraw at any time and for any reason without prejudice to their medical care. Randomization procedures and randomization lists were deposited in a sealed envelope before recruitment of the first patient. Single decoding is available for each subject in sealed envelopes. The envelopes containing information about group affiliation are opened by an authorized study team member at the last possible time (at the earliest after complete baseline evaluation).

**Table 1 T1:** In- and exclusion criteria.

**Inclusion criteria**	**Exclusion criteria**
• Pending chemotherapy (neo-/adjuvant)	• Significant comorbid conditions contraindicating physical activity
• Diagnosed breast cancer	• Cognitive dysfunction, defined by subjective or diagnostic deficits in attention, memory, executive function and/or visual construction before the start of chemotherapy, as well as any known history of cognitive disorder at the baseline screening.
	• In tests without clear ranges of reference values for cognitive impairments in performance, cut-offs will be defined using >1,5 SD from normative data. Cognitive impairment therefore is defined by > 1,5 SD in two tests at baseline assessment.
• Eastern Cooperative Oncology Group (ECOG) performance status of 0 or 1	• Vigorous physical activity of >300 min weekly within the last 6 months before diagnosis of breast cancer (Evaluated by training anamnesis)
• Age ≥ 18–70 years	• Patients unwilling to complete endurance exercise or complete all questionnaires related to the study
• Adequate hematologic function Platelet count > 50 × 10^∧^9/L Hemoglobin > 8 g/dL	• Past or current history of other malignant neoplasms other than breast cancer in the last 5 years
• No motorical dysfunction leading to the disability to perform endurance exercise according to protocol	• Coronary heart disease
• Signed informed consent prior to randomization	• Left bundle branch block
• Fluid in German	• Chemotherapy or radiation with other indications than breast cancer diagnosis
	• Current pregnancy or plans to become pregnant within the next 3 years
	• Neurodegenerative disease

All assessments are conducted at three main time points (t_0_, t_1_, t_2_) in both groups.

t_0_ (Pre): Before first chemotherapy within ± 14 days.t_1_ (interim): After 6 months ± 14 days.t_2_ (post): After 12 months ± 14 days (end of intervention).

For participants in all groups, clinical assessments during the intervention period are additionally performed at least every second month and at each clinical visit (usual care).

### Data Collection and Timeline/Testing Procedure

Data are collected at baseline (t_0_), after 6 months of intervention (t_1_) and after 12 months of intervention (t_2_). The patient's medical record and intended therapy, demographic (age, sex) and anthropometric data (weight, height, BMI), past medical history and current medication are collected at the start. Furthermore, the primary outcome and all secondary outcome measurements of the study are captured before the first therapy session. After 6 months of intervention (t_1_), an interim exercise test is conducted to adapt the exercise workload in Arm A and in Arm B for equality. At (t_2_) the primary outcome measures and all secondary outcome measures are re-assessed. A follow-up period of 12 and 24 months is provided after the end of the intervention. The follow-up assessments therefore are parameters assessed within the clinical routine amended by the questionnaires used to assess quality of life and activity level.

A detailed study schedule is presented in Supplementary Appendix 1.

All assessments except exercise testing are performed at the Kepler University Hospital, Linz (AUT). At (t_0_), (t_1_), and (t_2_). All blood samples are drawn and stored at minus 85°C at the Kepler University Hospital Linz. Analyses of cancer-related pro- and anti-inflammatory biomarker samples are performed at the Sports University of Cologne.

### Exercise Testing

Incremental exercise tests with a one-minute step duration are conducted on a calibrated bicycle ergometer (Corival cpet, Lode BV Medical Technology, NL) (70). Before each test, the breathing gas analyser (Vyntus CPX, CareFusion Germany 234 GmbH, D) is calibrated for volume and O_2_/CO_2_ concentration according to the manufacturer's guidelines. Every participant is seated for about 1–2 min on the ergometer while preparing one ear lobe for blood-testing. During exercise tests, respiratory gas exchange is recorded, and heart rate is measured continuously using the ECG system KISS MULTILEAD (GE Medical Systems Information Technologies GmbH, D). Lactate concentrations are determined in capillary blood taken from the ear lobe at rest and at the end of each increment until exhaustion and therefore end of testing.

### Groups and Description of Intervention

#### Exercise Intervention Arm (A)

Participants randomized to the exercise arm are motivated to fulfill the general physical activity recommendations with a defined heart rate and material for strength training (folder and exercise video). The frequency and duration of the home-based exercise depends on individual circumstances but follows general suggestions.

American College of Sports Medicine (ACSM) has recommended the following physical activity for cancer survivors (69):

Take part in regular physical activity.Avoid inactivity and return to normal daily activities as soon as possible after diagnosis.Aim to exercise at least 150 min weekly with moderate intensity.Include strength training exercises at least 2 days per week.

The advised heart rate therefore is defined by the baseline exercise testing and adjusted after 6 months if necessary.

Additionally, group A is asked to perform a supervised HIIT at the Cardiomed Linz rehabilitation center once a week.

The high intensity exercise interventions are performed on a stationary bike (ergo_bike premium 8, daum electronic gmbh, D). An experienced and accredited therapy specialist supervises and supports the exercise interventions throughout the trial.

Participants perform alternating intervals of maximal power output P_max_ (measured by the exercise test) and rest in a ratio of 1:3. The duration of the P_max_ interval is 20 and 60 s for pause.

The HIIT program is set up in two cycles; one includes an enhancement of the weekly intervals and a recovery unit (3:1) (shown in Figure 2A). This cycle is followed by a stabilization cycle (4 weeks), in which the number of intervals is kept constant (shown in Figure 2B). The next cycle starts with a higher number of intervals and is enhanced over 3 weeks, followed by a recovery unit (3:1), and continued by another stabilization cycle (4 weeks). A schematic graphic of this periodized exercise regimen is shown in Figure 2 (71). After 6 months of intervention, a re-evaluation of the patient's performance is conducted as described above. The peak load of the intervals will be adapted according to the new P_max_ if any alteration in peak performance is observed.

**Figure 2 F2:**
[figure not shown]
Schematic representation of the amount of intervals for the first 6 month of intervention. HIIT is planned in 2 cycles, **(A)** Continual enhancement of the amount of intervals up to week 3 followed by one recovery week (3:1). **(B)** Stabilization cycle, which includes 4 weeks of a continual amount of intervals. Those stabilization cycles will be enhanced over time by the amount of intervals. This cyclic scheme will be maintained over the year of intervention period.

HIIT in week 1 is conducted with 8 intervals (see Figure 3) and enhanced to 10 intervals in week 2 and 12 in week three. The recovery units are adapted to the number of intervals. The following stabilization cycle includes 10 intervals over 4 weeks. The duration of the HIIT sessions therefore depends on the amount of intervals and ranges from 20 min at the beginning of the program to ~45 min at the end of the intervention.

**Figure 3 F3:**
[figure not shown]
Schematic representation of the HIIT for the first week of intervention. Warm-up exercise starts low at 20% P_max_ and will be increased in 5 increments up to 40% P_max_. Intervals will be performed at 100% P_max_ for 20 s and recovery intervals will be 60 s at 20% P_max_ giving a mean workload (P_mean_) of 40% P_max_ according to Tschakert and Hofmann (QUELLE). Overall workout duration is 20 min.

HIIT load is enhanced over time by increasing the amount of intervals and increased to a 2:1 ratio (rest to load) in the last 3 months, according to expected training adaptations.

#### Control Arm (B)

Participants in the control arm receive usual care and physical activity recommendations following regular procedures. Patients are examined during clinical visits. The control group receives the same physical activity recommendations (see above) as the intervention group except any heart rate suggestions.

#### Documentation of Exercise Intervention

Center based exercise interventions in arm A and all home-based physical activity (arm A and B) are recorded by a “Garmin Forerunner 45s” (with “Garmin Connect”) in combination with a chest strap. Heart rate, frequency, and duration of home exercises are documented in a digital activity diary provided on the online platform “www.trainingpeaks.com”. Patients perform low intensity endurance exercise at home with any type of sports equipment or outdoors independently.

### Study Endpoints

#### Primary Endpoint

The primary endpoint is the difference from baseline (t_0_) to completion of the exercise intervention (t_2_), in the California Verbal Learning Test (CVLT) mean scores and consists of the three (sub)scores “short-delay,” “long-delay” and “total-trials 1–5” of the CVLT. The CVLT is an instrument commonly used to evaluate the individual verbal learning and memory.

The test consists of two 16-word lists. The word list A is defined as the learning-list; word list B is used to interfere (interference-list). Word list A will be read aloud to the patient 5 times, then list B will read once. After that, the patients must recall as many words as possible from list A, afterwards the semantic recall follows. After 20 min, the patient is asked to recall again as many words as possible from list A, followed by a helping recall trail. For recalling, similar, semantic and phonematic distractions and categoric prototypes will be used. There are two normed settings available for baseline and t_2_.

The (sub)scores “total-trials 1–5” ascertains the learning curve for the first word list based on 5 rounds. The “short-delay” reports the delayed recall immediately after presentation and retrieval of the second word list (as interference) and without repeating the first list. The “long-delay” is testing the recall after ~20 min.

#### Secondary Endpoints

Further neuropsychological related endpoints distinguish by the variable attention and motor-speed, memory, executive functions, and visual construction.

To raise attention and psycho-motoric speed the subtest Digit Symbol Coding (of WAIS IV) is used, in which as fast as possible, symbols shall be written to different objects and the Trail Making Test A, in which numbers shall be put together in the correct order.

Memory function is captured with the subtests Logical Memory I & II (of WMS IV, memorizing texts immediately and after ~30 min). The subtest Digit Span backwards (of WAIS IV), Trail Making Test B/A (quotient of the processing times required for Trail Making Test B) and the “Regensburger-Wortflüssigkeits-Test” for word fluency (words with a special initial letter, words from a special category) measure executive functions.

At last, the subtest Block Design (of WAIS IV) in which patterns have to be recreated from a template with cubes is used to get information about the visual construction.

Secondary endpoints of physical activity and exercise related aspects are represented by performance changes obtained from exercise testing. Main variables are maximal oxygen uptake (VO_2max_) and maximal power output (P_max_), submaximal threshold values such as the first and the second ventilatory thresholds (VT_1_, VT_2_), body composition (body fat, muscle mass, Waist-to-Hip ratio, BMI) and the global physical activity questionnaire (GPAQ).

Additionally morphological changes of the heart will be objectified by strain-analyses. Speckle-tracking-echocardiography performed by Aplio-i900 (Canon) is implemented to evaluate possible chemotherapy related effects on the ventricular function.

Further patient-related endpoints like fatigue, emotional functioning/well-being, physical functioning/well-being, and QOL are measured by the Pittsburgh Sleep Quality Index (PSQI), Multidimensional fatigue inventory (MFI-20), Functional Assessment of Cancer Therapy-General (FACT-G, FACT-G/F), Beck-Depression-Inventar (BDI-II) and State-Trait-Anxiety Inventory (STAI).

Survival related endpoints are defined as the time from randomization to any signs of locoregional or metastatic recurrence or the appearance of secondary cancer or death, whichever occurs first - disease free survival (DFS) and time from randomization to death from any cause - overall survival (OS).

Endpoints of cerebral imaging are measured by Magnetic Resonance Imaging (MRI) and analyzed by “FreeSurfer” to show morphological signs of chemotherapy related effects on hippocampus volume. Cerebral images are acquired by a 3-Tesla Magnetom Trio Scanner (Siemens, Germany). For volume hippocampal measurement the automated volume-measurement software “FreeSurfer,” V.6.0 is used.

Laboratory endpoints, former connected to CRCI, are measured by pro- and anti-inflammatory biomarkers including Tumor necrosis factor alpha (TNF-α), Interleukin1 alpha,−1 beta,−6,−10 (IL-1α, IL-1β, IL-6, IL-10), C-reactive protein (CRP), Interleukin-1 receptor antagonist, (IL-1RA) and Neurotrophic and growth factors including Brain-derived neurotrophic factor (BDNF), Insulin like growth factor (IGF-1), Vascular Endothelial Growth Factor (VEGF) and Matrix-Metalloproteases (MMP). The primary endpoint and all secondary endpoints are summarized in Table 2.

**Table 2 T2:** Primary and secondary endpoints.

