#### Regression Analyses

The influence of exercise and exercise test results on overall survival and disease-free survival will be investigated by cox regression analyses. Multiple regression analyses will be used to investigate the influence of baseline characteristics and any specific findings during the intervention phase on the primary endpoints in group A.

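### The disease-free survival definition has no event for neoadjuvant patients whose tumour progresses locally or becomes inoperable before surgery

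*Protocol article*

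**What the plan says.** All references are to the protocol article.

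- **Endpoint.** Secondary Endpoints defines DFS as the "time from randomization to any signs of locoregional or metastatic recurrence or the appearance of secondary cancer or death, whichever occurs first". Table 2 lists DFS and overall survival as the survival-related endpoints.
- **Population.** Study Population and Recruitment describes the candidates as "Patients diagnosed with local breast cancer receiving neo-/adjuvant chemotherapy". The inclusion criteria in Table 1 require that chemotherapy is still to come and allow either setting.
- **Timing.** The baseline assessment is placed "Before first chemotherapy within ± 14 days". The allocation envelope is opened "at the earliest after complete baseline evaluation". Under Methods: "The exercise interventions start within the first week of chemotherapy and last for 12 months".
- **Follow-up.** Data Collection and Timeline/Testing Procedure: "A follow-up period of 12 and 24 months is provided after the end of the intervention".
- **Analysis.** Regression Analyses: "The influence of exercise and exercise test results on overall survival and disease-free survival will be investigated by cox regression analyses". Presentation of the Results adds Kaplan-Meier plots for time-to-event variables. Type I Error Adjustment makes all inference outside the three CVLT hypotheses descriptive.

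**The concern.** DFS presupposes a patient who is free of disease when the clock starts. That fits the adjuvant patients, whose tumour has been removed. It does not fit the neoadjuvant patients, who receive chemotherapy before surgery and are randomised with the tumour in place.

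The event list contains recurrence, second cancer and death. It does not contain progression of a tumour that was never removed, or failure to reach definitive surgery because of progression. A patient with either outcome is carried as event-free until something else on the list happens. The omission falls in the chemotherapy period, when the exercise programme is also running. At stake is whether the DFS curves and Cox models count early treatment failures in the neoadjuvant group at all, and at the right date.

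**Working it through.** The plan states no DFS event count, hazard ratio or power, so there is no figure to reproduce. The check sets the definition beside the population and timing, then sizes the gap under stated assumptions.

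**Step 1: when is a neoadjuvant patient randomised?**
- Lower bound: allocation is revealed no earlier than the end of the baseline evaluation, which is tied to the first chemotherapy with a 14-day window.
- Upper bound: exercise begins in the first week of chemotherapy, so allocation must be known by then.
- Neoadjuvant chemotherapy precedes surgery by definition. These patients are therefore randomised before surgery, with the primary tumour in place.

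**Step 2: which outcomes before surgery meet the event list?**

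| Outcome before surgery | Event under the written rule? |
|---|---|
| Death | Yes |
| Second cancer | Yes |
| New distant metastasis | Arguably, if metastatic recurrence is read loosely |
| Local or regional progression of the tumour in place | No, nothing has recurred |
| Progression that makes the tumour inoperable | No |

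**Step 3: is this repaired elsewhere?** No section of the article adds progression as an event, or treats the two settings separately in the Kaplan-Meier or Cox analyses.

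**Step 4: size.** N = 126 is from Results of Sample Size Estimations. The neoadjuvant share (30–70%) and the proportion of those patients with local or regional progression or inoperability before surgery (2–5%) are assumptions.

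Patients affected = N × share × proportion

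| Share | 2% | 5% |
|---|---|---|
| 30% | 126 × 0.30 × 0.02 = 0.8 | 126 × 0.30 × 0.05 = 1.9 |
| 50% | 126 × 0.50 × 0.02 = 1.3 | 126 × 0.50 × 0.05 = 3.2 |
| 70% | 126 × 0.70 × 0.02 = 1.8 | 126 × 0.70 × 0.05 = 4.4 |

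That is about 1 to 4 patients. If the proportion were as high as 10%, the upper corner would be 126 × 0.70 × 0.10 = 8.8.

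**Step 5: how much can DFS show in any case?** Follow-up is at most 12 + 24 = 36 months. Assuming 3–5% DFS events per year with no losses, expected events are 126 × 3 × 0.03 = 11.3 to 126 × 3 × 0.05 = 18.9. With 1:1 allocation, two-sided 5% and 80% power, the Schoenfeld formula gives 4 × (1.960 + 0.842)² / (ln 0.5)² = 31.4 / 0.480, or 66 events, to detect even a hazard ratio of 0.5. DFS is therefore imprecise under any definition.

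**The case against.** **The endpoint carries little weight.** Survival is not among the aims listed at the end of the Introduction, the sample size rests on the CVLT alone, and DFS results are declared descriptive. This stands, and it caps the importance of the point.

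**Most serious failures are still captured.** A reader might infer that the worst failures are scored as successes. The text does not support that. Deaths count, metastases during chemotherapy arguably count, and a local progression that later spreads is delayed rather than lost. What remains outside the list is isolated local or regional progression and inoperability.

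**There is one clock and one list.** A reader might also infer that the analysis mixes two time scales or two event definitions. It does not: origin and event list are the same for everyone. What differs by setting is the disease state at the origin and which listed events can occur early on.

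**No bias towards one arm is shown.** Randomisation balances the settings on average, and nothing in the document points to a preference for either arm. This stands for the comparison of arms. It does not make an unlisted event counted. It also does not protect the planned regression of DFS on exercise test results, which are not randomised. If fitness differs between patients before and after surgery, which is plausible but not stated, setting could confound that analysis.

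**The relative loss cannot be pinned down.** Dividing Step 4 by Step 5 gives 0.8/18.9 = 4% to 4.4/11.3 = 39%. That range pairs opposite extremes of assumed inputs and ignores the 15% drop-out the protocol expects, so no weight should be put on it.

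**Detail may sit in the full protocol or analysis plan.** This is fair for model strata and covariates, whose absence is not itself a fault here. It does not cover the definition. The article gives origin, event list and first-event rule in full, and an analysis plan that followed them would carry the gap forward.

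**Conclusion.** The point holds as a gap in a stated definition. Neoadjuvant patients are randomised with the tumour in place, and local or regional progression or inoperability before surgery is not a DFS event. These failures are missed, or dated to a later metastasis, second cancer or death, and the endpoint's name does not describe these patients at the time origin.

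The size is small in absolute terms: about 1 to 4 of 126 patients, resting wholly on an assumed 30–70% neoadjuvant share and 2–5% progressing. The effect is confined to a secondary, unpowered, descriptive endpoint. The CVLT primary analyses and overall survival are untouched. The documents do not support a claim that the gap favours either arm. It is worth correcting because the written rule, if followed, would misclassify events and the correction is inexpensive.

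**What to change.** In Secondary Endpoints and Table 2:

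1. Keep randomisation as the origin for all patients.
2. Rename the endpoint event-free survival and add one item to the existing event list: progression before surgery, or progression that prevents definitive surgery.
3. Present the descriptive Kaplan-Meier curves and Cox models by neoadjuvant or adjuvant setting, or stratify them by it. The intended therapy is recorded at the start (Data Collection and Timeline/Testing Procedure) and can supply this factor.

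Do not restart the clock at surgery for neoadjuvant patients, and do not limit the analysis to patients rendered disease-free. Either would select on an event after randomisation, remove the early failures at issue and break the randomised comparison.

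Cost: the endpoint name changes, and progression before surgery must be abstracted from the clinical record. The article does not say that setting is held as a coded variable, so it may have to be derived from the recorded intended therapy. Sample size and visit schedule are unaffected.
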